## Abstract

**Background:**

Modulating the microbiota in the large intestine of kidney transplant recipients through prebiotic supplementation may prevent infectious complications from occurring. To date, there have been no interventional trials which have investigated this novel treatment in kidney transplantation. The aim of PREBIOTIC is to assess the feasibility of performing a randomised controlled trial of prebiotics in reducing infections and gastrointestinal symptoms in kidney transplant recipients.

**Methods:**

Sixty kidney transplant patients will be recruited to a double-blind, placebo-controlled, randomised feasibility trial. Patients will be provided with prebiotic therapy or placebo for 4 to 6 weeks. Outcomes will include recruitment, adherence, tolerance, retention, laboratory parameters (including serum indoxyl sulphate, ρ-cresyl sulphate and stool collection), patients’ self-assessed quality of life, gastrointestinal symptoms and clinical outcomes.

**Discussion:**

This trial will assess the feasibility of prebiotic supplementation in kidney transplant recipients. Prebiotics not only may alter the gut microbiota and their inherent metabolism and production of uraemic toxins but also may prevent infections from occurring in kidney transplant recipients.

**Trial registration:**

Australian New Zealand Clinical Trials Registry number ACTRN12618001057279p. The date of registration was 25th June 2018, https://www.anzctr.org.au/Trial/Registration/TrialReview.aspx?id=375370&isReview=true.

## Introduction

### Background

Infections are a common complication following kidney transplantation, occurring in 40–65% of kidney transplant recipients in Australia and worldwide [1–3]. It is expected that the burden of infectious complications will continue to rise based on the growing prevalence of diabetes mellitus and the increasing potency of immunosuppressive regimens [4, 5]. It is therefore unsurprising that the Standardised Outcomes of Nephrology-Transplantation (SONG-Tx) initiative has identified infection as a core outcome that should be reported in all kidney transplant trials [6].

Over the last 5 years, emerging evidence has indicated that the gastrointestinal microbiota may play a role in the pathogenesis of infections in kidney transplant recipients [7–9]. The human microbiota are a collective of specialised communities of commensal, symbiotic and pathogenic micro-organisms (bacteria, archaea, fungi, protozoa and viruses) that colonise different sites and surfaces of the human body, of which the gastrointestinal tract has received the most intense investigation [10–12]. Various factors may influence the composition and diversity of the gastrointestinal microbiota including age, sex, medications, medical conditions and diet [13, 14]. Studies have indicated that gut dysbiosis in patients with chronic kidney disease may be associated with increased production of uraemic toxins, such as indoxyl sulphate (IS) and ρ-cresyl sulphate (pCS), which have been associated with intestinal inflammation, renal tubulointerstitial fibrosis and the progression of kidney disease [15, 16]. Gastrointestinal symptoms have also been shown to negatively impact quality of life in kidney transplant recipients [17].

Since the composition and diversity of the gastrointestinal microbiota may be modified by diet, it has been hypothesised that nutritional interventions, such as prebiotics (food sources that promote the growth of beneficial intestinal micro-organisms), probiotics (live micro-organisms that confer health benefits when ingested) and synbiotics (combined prebiotics and probiotics), may be a therapeutic opportunity to mitigate infectious complications in transplant recipients [13, 14, 18]. To the best of our knowledge, there have been no studies that have examined nutritional therapies in kidney transplant recipients. A meta-analysis of four studies (3 randomised controlled trials and 1 historically controlled trial) involving 246 liver transplant recipients has shown that administration of synbiotics resulted in appreciably lower rates of overall infection (relative risk [RR] 0.21, 95% *CI* 0.11–0.41, *I*^2^ = 1%), urinary tract infection (*RR* 0.14, 95% *CI* 0.04–0.47, *I*^2^ = 0%) and intra-abdominal infection (*RR* 0.27, 95% *CI* 0.09–0.78, *I*^2^ = 0%) [18]. The limitations of this review included moderate heterogeneity of the prebiotic and probiotic interventions, small sample sizes, short follow-up durations, restriction to only liver transplant recipients, inclusion of a non-randomised controlled trial and low certainty of evidence. Thus, there is an unmet need to assess the feasibility of establishing a randomised controlled trial in examining the effectiveness of prebiotic supplementation in preventing infections and gastrointestinal symptoms in kidney transplant recipients.

## Methods

### Aims and objectives

The aim of this study is to assess the feasibility of performing a randomised controlled trial of prebiotics in reducing infections and disruptive gastrointestinal symptoms in kidney transplant recipients. The primary objectives are to determine the following:This Prospective Randomised Evaluation of preBiotic In solid Organ Transplant recipients to prevent Infectious Complications (PREBIOTIC) study will be able to successfully recruit 60 patients within 6 months.Kidney transplant recipients will be adherent to prebiotic supplementation during the first 4 to 6 weeks following kidney transplantation.Prebiotic supplementation will be well tolerated by kidney transplant recipients during the first 4 to 6 weeks following kidney transplantation.Withdrawal of kidney transplant recipients will be minimal from a randomised controlled trial examining the safety and efficacy of prebiotic supplementation as an infection prevention strategy during the first 4 to 6 weeks following kidney transplantation.Kidney transplant recipients will be able to provide (in at least 80% of patients) two stool samples and two blood samples during the first 4 to 6 weeks following kidney transplantation to ascertain whether prebiotic supplementation improves dysbiosis.Prebiotic supplementation in kidney transplant recipients will result in improved quality of life during the first 4 to 6 weeks following kidney transplantation.Prebiotic supplementation in kidney transplant recipients will reduce the number of infections and infection-related hospitalisations during the first 4 to 6 weeks following kidney transplantation.

### Trial design

This study is a single-centre, parallel group, double-blind, randomised placebo-controlled feasibility trial (Fig. 1). Informed consent will be obtained from all participants. The study will be conducted according to the International Committee of Harmonisation (ICH) and good clinical practice (GCP) guidelines and reported according to CONSORT guidelines.

**Fig. 1 Fig1:**
[figure not shown]
PREBIOTIC study schema

### Setting and participants

Sixty acute kidney transplant recipient patients will be recruited from the Princess Alexandra Hospital kidney transplant ward (Brisbane, Queensland, Australia) over a 6-month period. The Princess Alexandra Hospital is the only kidney transplant unit in Queensland and is the largest kidney transplant unit in the Oceania region. To be eligible to participate in this trial, participants must satisfy all of the following criteria: receive a kidney transplant at the Queensland Renal Transplant Service, be aged ≥ 18 years and be able to provide informed consent. Patients will be excluded from participation if they meet any of the following criteria: have received radiation to the bowel and/or large bowel resection, medically diagnosed and active inflammatory bowel disease, unwilling or unable to meet the requirements of the protocol and other medical, social, cultural and/or linguistic reasons negatively affecting their adherence to the protocol, at the discretion of the investigators.

### Participant identification and recruitment process

Patients will be provided with written and verbal information about the study while an inpatient in the transplant ward. They will be given the opportunity to ask questions, to take the information home with them when they leave hospital and to discuss it with friends, family or others. They will be able to provide consent at one of their routine clinic visits in the early post-discharge period. This will ensure that the patients are physically and mentally well and stable and thereby able to fully consider their participation in the study. Once they have consented to participate in the study (usually between day 5 to day 12 following acute kidney transplant), participants will commence the prebiotic powder or placebo suspended in water daily for 4 to 6 weeks. The initial dosage will be 7.5 g daily for the first 2 weeks, thereafter increasing to 15 g daily for the final 2 to 4 weeks of the study.

### Treatment

This trial will consist of two arms: (1) green banana-resistant starch (prebiotic supplement) and (2) waxy maize (matched, identical placebo).

#### Intervention — green banana-resistant starch

The active intervention in this study will be green banana-resistant starch multi-fibre. This is a functional food product structurally resistant to digestion in the small intestine [19]. When resistant starches reach the large intestine, the polymers can be deconstructed and fermented by the resident microbiota. The beneficial effects from these products include a laxative effect promoting regularity of bowel motions and the capacity to promote the growth of select commensal microbes, in addition to beneficial effects reported on lipid-based biomarkers in subjects with type 2 diabetes mellitus.

#### Comparator — waxy maize

The comparator (control) in this study will be waxy maize, which is primarily comprised of branched starch polymers (amylopectin) that are more readily digestible in the small intestine. As such, much of the placebo should be digested proximal to the large intestine and will have limited impacts on the large intestinal microbiota.

### Concomitant treatment

All other treatment, including medications, will be as per standard care for the patient.

### Randomisation

Participants will be randomly assigned in a 1:1 ratio to receive either prebiotic or placebo. The randomisation schedule will be prepared by a researcher not involved with treatment allocation. Standard blocking and stratification will be used to ensure between-group balance of size and patient characteristics, including age (< 65 years, ≥ 65 years) and sex. A blinded allocation list will be maintained in an Excel spreadsheet on a secure server not accessible to staff involved in study recruitment and data collection.

### Blinding

Participants, caregivers, treating physicians and surgeons, laboratory staff and members of the study team will be blinded to the treatment. Only the statistician not involved with recruiting patients in this study will be aware of the product allocation sequence.

### Primary and secondary outcomes

The primary outcome of this study is feasibility of recruitment which will be defined as at least 80% of eligible subjects recruited to the study.

The secondary outcomes will include the following:Timeliness of recruitment

This will be assessed as the ability to successfully recruit 60 patients within 6 months.b)Adherence

This will be assessed as the proportion of participants adherent to prescribed study therapy (intervention or placebo) over the period of the study. Adherence will be defined as having used 80% of more of the prescribed study therapy, calculated by the % of the expected weight of the product returned divided by the initial weight of study therapy.iii)Tolerance

This will be assessed as the proportion of patients who continue the prebiotic supplementation. Tolerance will be defined as 80% of the recruited patients taking the prescribed study therapy during the study period.iv)Gastrointestinal symptom assessment

The gastrointestinal symptom assessment will be assessed as the changes in the Gastrointestinal Symptom Rating Scale score from baseline compared with the score at the time of the completion of the PREBIOTIC trial.e)Retention

This will be assessed as the proportion of patients who remain in the PREBIOTIC study for the entire study period.f)Laboratory samples

There will be two aspects to this outcome. The first part will examine the proportion of participants providing two stool samples at designated times (during the first week and between 4 and 6 weeks post-kidney transplant) with sufficient material to assess gut microbiota (stool sample analysis via shotgun metagenomic sequencing to a target depth of 3 Gbp using NovaSeq 6000, 2 × 150 base pair, paired-end chemistry). The second part of this outcome will assess the proportion of participants providing two blood samples for serum indoxyl sulphate and p-cresyl sulphate measurement at designated times (during the first week and between week 4 to week 6 post-kidney transplant).g)Quality of life

This will be assessed as the changes in the overall quality of life score (measured by EQ-5D survey) from baseline compared with the score measured at the completion of the PREBIOTIC trial.h)Infectious events

This will be assessed as the proportion of patients who develop at least one infectious event requiring hospital admission or antimicrobial therapy. Infectious adverse events of special interest would include the following:

Urinary tract infectionsGastrointestinal infectionsRespiratory infections (e.g. community or hospital acquired)Opportunistic infections (e.g. cytomegalovirus, BK virus)Skin or soft tissue infectionsCentral nervous system infectionsi)Safety

A serious adverse event (SAE) will be defined as any event/reaction that results in death, is life-threatening, requiring hospitalisation or prolongation of exisiting hospitalisation and resulting in persistent or significant disability or incapacity. All SAEs will be documented and reported to the ethics committee for review.

Prebiotic supplementation may also increase serum potassium particularly during the early days following kidney transplantation. The hyperkalaemia may also be related to constipation from prebiotic supplementation. Nevertheless, the participant’s serum potassium will be checked as per usual clinical routine (daily for the first 3 weeks then thrice weekly thereafter). Patients may be advised to stop the prebiotic temporarily if their serum potassium levels increase above 6.0 mmol/L.

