### Planned analysis

As this is a feasibility study, data will be analysed via descriptive statistics, expressing frequencies (percentages) for categorical data, mean ± standard deviation for continuous normally distributed data or median (interquartile range) for continuous non-normally distributed data. In addition, confidence intervals will be presented for all descriptive statistics. Outcome measures and the corresponding statistical measures are shown in Table 2. Analysis will be performed on an intention-to-treat basis. Patients discontinuing the study drug for whatever reason will be encouraged to continue follow-up in the trial. The null hypothesis will be rejected at the 0.05 level. The statistical analyses will be performed using Stata (version 14, 2016, Statacorp, College Station, TX, USA).

**Table 2 Tab2:** Outcomes and corresponding measures

Outcome	Measure
Proportion of eligible patients who agree to take part in the study	% (95% CI)
Ability to successfully recruit 60 patients within 6 months	% (95% CI)
Proportion of participants adherent to prescribed study therapy (intervention or placebo) over the period of the study	% (95% CI)
Proportion of patients who continue to the prebiotic supplementation	% (95% CI)
Mean changes in the Gastrointestinal Symptom Rating Scale	Mean change (SD)
Proportion of patients who withdraw from the PREBIOTIC study	% (95% CI)
Proportion of participants providing two stool samples at designated times (the first week and between week 4 to week 6 post-kidney transplant) to assess gut microbiota changes	% (95% CI)
Proportion of participants providing two blood samples at designated times (the first week and week 6 post-kidney transplant)	% (95% CI)
Changes in the overall quality of life (measured by EQ-5D survey)	Mean change (SD)
Proportion of patients with at least one infectious event	% (95% CI)

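### The tolerance outcome has conflicting denominators: the measure concerns patients continuing the prebiotic, but the 80% threshold is set on all recruited patients

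*Protocol article*

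**What the plan says.** Four statements in the protocol article bear on tolerance.

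- **Objective** (Aims and objectives): "Prebiotic supplementation will be well tolerated by kidney transplant recipients during the first 4 to 6 weeks following kidney transplantation".
- **Measure** (Primary and secondary outcomes, Tolerance): "This will be assessed as the proportion of patients who continue the prebiotic supplementation".
- **Threshold** (the next sentence of the same item): "Tolerance will be defined as 80% of the recruited patients taking the prescribed study therapy during the study period".
- **Reporting** (Planned analysis, Table 2): "Proportion of patients who continue to the prebiotic supplementation", as a percentage with 95% CI. The row names no threshold and no denominator.

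The adherence item just above uses the same term for the product and spells it out: "the proportion of participants adherent to prescribed study therapy (intervention or placebo) over the period of the study". Under Randomisation, "Participants will be randomly assigned in a 1:1 ratio to receive either prebiotic or placebo", so the planned 60 patients give 30 per arm.

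**The concern.** The objective, the measure and Table 2 all name the prebiotic. The threshold names recruited patients and study therapy, and the adherence item shows that study therapy covers both products. An analyst who follows the threshold sentence to the letter divides by 60. One who follows the measure or Table 2 may divide by 30.

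The choice matters because, on the protocol's own account (Treatment), the two products behave differently. The resistant starch passes to the large intestine and is fermented there; waxy maize should mostly be digested before that point. Continuation on waxy maize therefore says little about whether patients can tolerate resistant starch, yet it supplies half of the pooled denominator. At stake is whether a statement that the tolerance criterion was met answers the stated objective. The Discussion gives that answer weight, since it says that poor tolerance would seriously undermine a formal trial.

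**Working it through.** **Inputs from the protocol article.** Total 60 patients (Setting and participants; Sample size); 1:1 allocation, so 30 per arm; threshold 80% (Tolerance item).

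**Inputs assumed.** The article gives no continuation rates by arm. I take true prebiotic continuation as 60%, 65% or 70% and placebo continuation as 85% to 100%, and show the range.

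**1. The plan's own precision figure.** Sample size states ±11% for 60 patients at 80%. The Wald half-width is 1.96 × √(0.8 × 0.2 / 60) = 10.1 points. With a continuity correction, adding 1/(2 × 60) = 0.83 points, it is 10.95. The exact (Clopper-Pearson) interval for 48/60 is 67.7% to 89.2%, an average half-width of 10.8. The stated 11% is reproduced by the corrected or exact method. It refers to the recruitment rate and does not depend on this point, but it shows the precision that a denominator of 60 gives.

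**2. What the literal threshold needs.** 0.80 × 60 = 48 patients continuing. The smallest prebiotic count that suffices is 48 minus the number continuing on placebo:

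| Placebo continuing | Prebiotic needed |
|---|---|
| 30/30 | 18/30 (60%) |
| 29/30 | 19/30 (63%) |
| 28/30 | 20/30 (67%) |
| 27/30 | 21/30 (70%) |

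The exact 95% CI for 18/30 is 40.6% to 77.3%, wholly below 80%.

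**3. How often each rule is met.** Let X ~ Binomial(30, p_prebiotic) and Y ~ Binomial(30, p_placebo), independent. The pooled rule is met with probability P(X + Y ≥ 48) = Σₓ P(X = x) · P(Y ≥ 48 − x). The arm-only rule uses 0.80 × 30 = 24 and is met with probability P(X ≥ 24).

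| True prebiotic | Pooled, placebo 85% | Pooled, 90% | Pooled, 95% | Pooled, 100% | Arm-only (≥24/30) |
|---|---|---|---|---|---|
| 60% | 11% | 22% | 37% | 58% | 1.7% |
| 65% | 22% | 38% | 58% | 78% | 5.9% |
| 70% | 39% | 58% | 77% | 92% | 16.0% |

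**4. Precision if the prebiotic arm is the denominator.** An observed 24/30 has an exact 95% CI of 61.4% to 92.3%, a half-width of (92.3 − 61.4)/2 ≈ 15 points.

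The arm-only rule is not sharp either. At a true rate of exactly 80% it is met 60.7% of the time, as expected of a point-estimate threshold in 30 patients.

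**The case against.** **Pooling is not the only reading.** The sentence before the threshold, Table 2 and the objective all name the prebiotic, so the authors may have meant the prebiotic arm throughout. This stands in part: the firm finding is a conflict between measure and threshold, not a settled intention to pool. The word prebiotic does not resolve it, because Table 1 also uses it for the dosing of all blinded participants.

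**A reader might infer that good placebo continuation could produce a decision to proceed despite a poorly tolerated prebiotic.** The document does not support that. The primary outcome is recruitment, tolerance is one of several secondary outcomes, and no progression rule is written. The Discussion says only that a successful study will inform a larger trial. The probabilities above are chances of meeting the stated tolerance criterion, not of a decision.

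**A reader might also infer that a failing prebiotic arm would stay hidden.** That does not follow. Nothing bars reporting by arm, Table 2 names no arm for any outcome, and the gastrointestinal symptom score and adverse events are collected separately. The fault is narrower: the criterion as worded does not depend on the arm that the objective is about.

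**Adherence is not in error.** "Proportion of participants adherent to prescribed study therapy (intervention or placebo) over the period of the study" can simply mean each participant's assigned product, and measuring adherence in both arms suits a placebo-controlled feasibility trial. Its 80% is a per-participant amount judged by powder weight, so it also differs from continuation, although the two overlap.

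**The probabilities depend on assumptions.** This stands. At 65% on prebiotic, the pooled figure runs from 22% to 78% according to the placebo rate alone. The gap from the arm-only rule remains throughout that range.

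**Conclusion.** The concern holds as an inconsistency that should be fixed. The tolerance measure and the tolerance threshold point to different populations, and the literal threshold can be met when the prebiotic arm falls well short of 80%. The 18/30 example is pure arithmetic and needs only 30 per arm and full continuation on placebo. The probabilities rest on assumed continuation rates and on independence between patients.

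The consequence is a potentially misleading claim that the tolerance criterion was met. The primary outcome and the sample-size basis are untouched. Because this is a definition that the article does state, a later analysis plan following it to the letter would inherit the problem.

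**What to change.** In Primary and secondary outcomes, state tolerance as the proportion of participants randomised to the prebiotic who are still taking their assigned product at the end of treatment. Apply the 80% threshold to that arm. Report the placebo proportion beside it, each with a 95% CI. Reword the tolerance row of Table 2 to match. Settle the wording before any unblinded data are seen, since the choice of denominator could decide whether the criterion is met.

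The change is to wording only, with no extra patients or data. Its cost is precision: about ±15 points with 30 patients, against about ±10 to 11 with 60. The interval should therefore be read alongside the threshold, because 24/30 just meets 80% while its lower limit is 61.4%.

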### Data collection

Data will be entered into Microsoft Excel during the course of the feasibility study, and data will be recorded only by investigators of the study. This system will help ensure compliance with medical data privacy, security and good clinical practice regulations. Data will be stored in password-protected files for 15 years and then destroyed. Physical copies of data will be kept in a locked filing cabinet. The data to be collected in this study are depicted in Table 1.

**Table 1 Tab1:** Data collection schedule and parameters to be collected

		Wk0	Wk2	Wk4	Wk6
**Patient information**	Consent and patient demographics	X			
	Medical history	X			
	Medications	X	X	X	X
	Infection risk	X			
	Immunological risk	X			
	Transplant history	X			
	Transplant course specifically documenting infection events		X	X	X
**Standard care biochemistry**	Full blood count Urea and electrolytes Fasting blood glucose HbA1c	X	X	X	X
**Uremic toxins**	Total serum IS	X			X
	Free serum IS	X			X
	Total serum pCS	X			X
	Free serum pCS	X			X
**Gut microbiota**	Bristol stool evaluation and stool sample collection	X	X		X
**Inflammatory markers**	C-reactive protein	X			X
**Quality of life (EQ-5D)**		X			X
**Prebiotic dose commencement**		X	X		
**Prebiotic dose escalation**			X		
**Gastrointestinal symptoms (GSRS)**		X	X		X
**Compliance**	Weight of powder				X
**Serious adverse events**			X	X	X
**Adverse events**			X	X	X

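### The sample-provision windows are counted from transplant and cannot be reconciled with the consent timing and the Table 1 schedule, so the outcome partly measures when patients consent

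*Protocol article*

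**What the plan says.** All references are to the Protocol article.

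- **Aims and objectives.** Recipients should be able to provide, "in at least 80% of patients) two stool samples and two blood samples", within the first 4 to 6 weeks after transplantation. No first-week requirement appears here.
- **Primary and secondary outcomes, Laboratory samples.** Stool samples count if given "at designated times (during the first week and between 4 and 6 weeks post-kidney transplant". Blood samples for indoxyl sulphate and p-cresyl sulphate count if given "at designated times (during the first week and between week 4 to week 6 post-kidney transplant". The two proportions are separate aspects of one secondary outcome.
- **Participant identification and recruitment process.** On consent, the article says "They will be able to provide consent at one of their routine clinic visits in the early post-discharge period". Study product starts once consent is given, "usually between day 5 to day 12 following acute kidney transplant", and is taken for 4 to 6 weeks, with the dose increase after the first 2 weeks.
- **Data collection, Table 1.** Consent is at Wk0. The row "Bristol stool evaluation and stool sample collection" is marked at Wk0, Wk2 and Wk6. The uraemic toxin rows are marked at Wk0 and Wk6. None of these is marked at Wk4. Dose commencement is marked at both Wk0 and Wk2, and escalation at Wk2. The time origin of the weeks is not stated.
- **Planned analysis, Table 2.** The blood outcome is given as "two blood samples at designated times (the first week and week 6 post-kidney transplant", so the second time is week 6 rather than weeks 4 to 6.

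**The concern.** The outcome is defined on a clock that starts at transplant. Consent, dosing and apparently the visit schedule run on a clock that starts some days later. A participant who gives every sample the schedule asks for could still be scored as not having provided samples at the designated times.

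Sample provision is listed among the objectives with an 80% threshold, and the study is meant to inform a large multicentre trial. If the windows are applied as written, late consent is counted as failure to provide samples. If analysts set the windows aside, what counts as compliant is decided after the data are seen. In neither case does the percentage cleanly answer whether recipients can give these samples.

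**Working it through.** **The plan's own figure.** The only calculated figure is the precision statement for recruitment: 60 subjects, 80%, plus or minus 11 points. The Wald half-width with continuity correction is 1.96 × √(0.8 × 0.2 / 60) + 1/120 = 0.1012 + 0.0083 = 0.1095, so the figure reproduces. It concerns recruitment and is not affected by what follows.

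**Inputs.** Usual consent and start on day 5 to 12 (recruitment section). First window up to day 7, and second window day 28 to 42, after transplant (outcomes section). Samples at Wk0 and Wk6 (Table 1). Product for 4 to 6 weeks, i.e. 28 to 42 days (recruitment section).

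**First window.** A research sample taken at or after consent falls in the first week only if consent is on day 5, 6 or 7. That is 3 of the 8 usual days; days 8 to 12, the other 5, are too late. The article gives no distribution of consent days, so the share of patients has to be assumed:

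- even spread over days 5 to 12: 3/8 = 37.5% can comply;
- even spread, with the first week ending on day 6: 2/8 = 25%;
- linearly early-skewed, weights 8, 7, …, 1: (8 + 7 + 6)/36 = 58%;
- nearly all consent by day 7: close to 100%.

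Reaching 80% of 60 would need 48 participants consenting by day 7.

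**Second window if Wk0 is consent or first dose.** Sample day = consent day + time on study.

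| Last sample taken at | Day after transplant | Usual consent days inside day 28–42 |
|---|---|---|
| start + 28 days | 33–40 | 8 of 8 |
| start + 35 days | 40–47 | 3 of 8 |
| start + 42 days (Wk6) | 47–54 | 0 of 8 |

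The Wk6 sample is therefore at 6.7 to 7.7 weeks, 5 to 12 days late for everyone in the usual range. It is also outside the 4-to-6-week period named in the 80% objective. The timing that would fit, 4 weeks after start, has no stool or toxin collection in Table 1.

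**Second window if Wk0 is transplant.** Wk6 is day 42, just inside the window. But the Wk0 consent and samples then fall on the day of transplant, before the usual consent on day 5 to 12. Escalation at Wk2 is day 14, which is 14 − 12 = 2 to 14 − 5 = 9 days after the start of product, whereas the recruitment section gives 2 weeks. Those two passages would need to be reconciled.

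**Result.** Each origin satisfies some passages and contradicts others. Neither reconciles the recruitment section, the outcome definition and Table 1.

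**The case against.** The strongest reply is that Table 1 may run from transplant. Dose commencement is marked at both Wk0 and Wk2, which suits a start between those visits. Wk6 is then day 42 and agrees with Table 2. A participant starting on day 5 to 12 and stopping at day 42 has 30 to 37 days of product, within 4 to 6 weeks. On that reading everyone can meet the second window. This stands as a possible reading, so failure of the second window is not certain. It does not remove the conflict, because it puts consent and the first samples before the recruitment section allows, and it leaves the first-week problem where it was.

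It can also be said that the first week means the first study week. The wording could bear that, but one phrase would then use two time origins, which is itself a reason to state them.

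Other replies stand. The usual range of consent days is not a limit, and its distribution is unknown. The 80% objective does not mention the first-week window. A third stool sample does not contradict an outcome that counts two, and week 6 in Table 2 lies within weeks 4 to 6; both are minor points of clarity. Stool and blood are deliberately separate aspects, so a joint proportion of participants giving all four samples is not required.

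**Conclusion.** The inconsistency is real and follows from the article's own figures. Five of the eight usual consent days are too late for a first-week sample. The Wk6 sample falls on day 47 to 54 if Wk0 is consent or first dose, which the consent and escalation rows suggest. As written, the outcome would partly record consent timing and could understate how feasible sampling is.

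A reader might go further and infer that most participants cannot comply and that the 80% target must fail. The documents do not support that. Complete failure of the second window needs Wk0 to be consent and the last sample to be taken at exactly 6 weeks, and the article states neither an origin nor a tolerance. The 37.5% figure needs consent days to be evenly spread, for which there is no evidence.

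The severity is moderate. The outcome is secondary and descriptive, and the primary outcome and the sample size of 60 are untouched.

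**What to change.** State the time origin of the weeks in Table 1. Define both sample windows on the study clock: the first sample after consent and before the first dose, the second at the end-of-treatment visit within a stated tolerance. Use that one definition in the objectives, the outcome text, Table 1 and Table 2, and say which of the three scheduled stool samples count towards the two. Stool and blood proportions can stay separate.

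The cost is wording and a table edit, with no added samples. The small downside is that samples are no longer tied to a fixed time after transplant. With usual consent on day 5 to 12 and 4 to 6 weeks of product, the second sample could fall anywhere from day 5 + 28 = 33 to day 12 + 42 = 54, so the actual day after transplant should be recorded and reported with the results.
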